## Study aims & hypotheses

2

In Aim 1, we will establish whether psychosocial stress increases levels of peripheral inflammation and levels of glutamate in fronto-cingulate-limbic circuits in adolescents with depression.

In Aim 2, we will define TNR based on whether depressed adolescents exhibit at least a 50% reduction in CDRS-R scores after 12 weeks of SSRI treatment. We will compare TNR versus non-TNR groups on TSST-related changes to inflammatory cytokines and glutamate. We will also test whether TSST-related changes in glutamate before and after SSRI treatment mediate the associations between TSST-changes in cytokines at baseline and TNR status (binary outcome). We will also explore models using depression severity as dimensional outcomes instead. We hypothesize that compared to non-responders, responders will show greater stress-induced increases in cytokines and glutamate, as well as stronger positive associations between cytokines and glutamate in threat neurocircuitry.

In Aim 3, we will characterize 18-month trajectories in adolescent depression from behavioral, inflammatory, and neural indicators of threat to social stress. Seven repeated clinical assessments over 18 months will support identifying depression trajectory subgroups (e.g., persistent depression, gradual remission, etc). For binary outcomes (diagnosis of depression), we will use information from clinical interviews to determine remission, relapse, or recurrence status at each timepoint. For dimensional outcomes, we will use symptom severity scores. We hypothesize that increased levels in indicators of sustained threat before and after SSRI treatment, as well as severity of past and ongoing life stress, will predict increased likelihood of experiencing chronic and unremitting depression over 18 months.

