For all of the statistical analyses testing these hypotheses, potential demographic (e.g., age, gender), clinical (e.g., age of depression onset, number of comorbidities, presence of childhood trauma), or biological (e.g., percentage of gray matter in MRS voxel) covariates will be included if they are correlated with our outcome variables*.* Statistical significance will be set at α = 0.05. We will apply false discovery rate (FDR) correction as appropriate. In all simulation analyses for estimating sample size based on 1-β = 0.8, effect sizes (*r* or η2 or mean ± SD) were based on preliminary data or cited literature. For the hypotheses in Aims 2 and 3 that require logistic ridge regression analysis, we plan to sample 90% data as the training set and 10% as the testing set across 10 iterations; power was therefore calculated based on 90% of the sample after accounting for attrition (*N* = 108). We will put in rigorous effort to minimize missing data, including scheduling sessions around families’ availability, repeating scans when data were not useable due to movement or scan/user error, and providing bonus incentives for completing all follow-up assessments. For all longitudinal analyses, we will use flexible modeling approaches that allow individuals who provide at least one assessment to be included in our estimation of the effects of interests.

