### Trier Social Stress Task (TSST)

3.6

A modified version of the Trier Social Stress Task (TSST) will be administered at T1V2 and T2V2. This adapted TSST involves no deception and follows procedures similar to those used by our group in adolescent populations (Ho et al., 2020; Kircanski et al., 2019; Miller et al., 2019). Following the first set of brain imaging acquisitions and the first blood sample collection, participants will be instructed by an experimenter that they will be completing a stress test. There will be two versions of the stress test: a five-minute arithmetic task or a five-minute speech task (regardless of the task, participants will be given 5 minutes of prep time beforehand). Participants will be randomly assigned one of the two stress tests at T1 and will be administered the second stress test at T2 to minimize habituation with repeated testing and ensuring that the order of the two tests are counterbalanced across the sample.

Upon arrival to the session, before, and after the TSST, participants will provide ratings of ten mood states (*Excited, Afraid, Confused, Sad, Energetic, Angry, Happy, Tired, Tense)* based on the Positive and Negative Affect Schedule (PANAS; Crook et al., 1998) on a visual analogue scale from 0 to 10. These ratings will be used as tertiary outcome measures of behavioral responses to social stress. During administration of the TSST, we will also collect saliva samples repeatedly to explore changes in stress hormones before and after an acute stressor. Five saliva samples, each collected approximately 10 minutes apart, will be collected using the SalivaBio Oral Swab Method (Salimetrics, LLC) during the TSST protocol, from which we plan to assay cortisol production. After completing the TSST, participants will complete the remaining scans and provide a secondary blood sample approximately 120 minutes after the first blood sample and then provide a final saliva sample. Additionally, it is possible that secondary stress and anxiety may affect cytokine and CRP levels at Time 1, as this will be the first time most of the participants will have undergone an MRI scan; however, our primary measures of inflammation and glutamate are *within-person differences* before and after the TSST. We will also consider using the PANAS ratings of mood states as covariates in sensitivity analyses.

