### Magnetic resonance spectroscopy (MRS)

3.10

To characterize neurometabolic data, we will implement single-voxel (SV) magnetic resonance spectroscopy (MRS) imaging before and after the TSST. We will utilize the sLASER sequence for metabolite detection *in vivo*. A custom-made developed excitation pulse (EB 2000E, 4 ms) will be used for X slice selection and four refocusing pulses will be used for Y and Z slice localization (Kaiser et al., 2022) and VAPOR water suppression will be used. Optimization of transmit gain and higher order shimming will be performed prior to MRS acquisitions for each voxel of interest, including the rostral anterior cingulate cortex, dorsal anterior cingulate cortex, and the left and right hippocampus.

All metabolite concentrations will be estimated using fitting in LCModel (Provencher, 2009) and expressed as ratios relative to total creatine (i.e., creatine and phosphocreatine) as these levels are relatively high and stable across different tissue types in the brain and, thus, often used as an internal reference standard. Only voxels that have relative Cramer-Rao lower bounds (CRLBs) < 25% for the metabolite of interest will be considered in further analysis. Finally, the effects of fluid within each voxel will be corrected by dividing the metabolite concentrations by the fraction of non-fluid components (i.e., WM and GM). Given the dynamic cycling between glutamine and glutamate (extracellular glutamate is converted into glutamine in astrocytes before being released and taken up by neurons where it is synthesized into either glutamate or GABA), we will also consider the total sum of glutamate and glutamine (Glx), and the ratio of glutamine to glutamate, as complementary indices of glutamate metabolism (Brennan et al., 2017; Cooper et al., 2021).

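### Voxel grey-matter percentage is kept only if it correlates with the outcome, which will usually drop it where glutamate change is a mediator or predictor; the likely cost is a small loss of precision

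*Protocol article*

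**What the plan says.** Section 2 (Study aims & hypotheses) of the protocol article gives a single covariate rule that applies "For all of the statistical analyses testing these hypotheses". Under it, "biological (e.g., percentage of gray matter in MRS voxel) covariates will be included if they are correlated with our outcome variables".

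The same section gives glutamate different roles in different analyses:

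- **Aim 1:** "we will establish whether psychosocial stress increases levels of peripheral inflammation and levels of glutamate in fronto-cingulate-limbic circuits". Glutamate is the dependent variable.
- **Aim 2, group comparison:** "We will compare TNR versus non-TNR groups on TSST-related changes to inflammatory cytokines and glutamate". Glutamate change is again the dependent variable.
- **Aim 2, mediation:** glutamate change is to "mediate the associations between TSST-changes in cytokines at baseline and TNR status (binary outcome". Glutamate is the mediator and non-response the outcome.
- **Aim 3:** indicators of sustained threat, the neural ones among them, "will predict increased likelihood of experiencing chronic and unremitting depression over 18 months". Clinical course is the outcome.

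Two further passages bear on tissue mix. Section 3.10 (MRS) expresses metabolites relative to total creatine and says that "the effects of fluid within each voxel will be corrected by dividing the metabolite concentrations by the fraction of non-fluid components", meaning white plus grey matter. Section 3.6 (TSST) says that the "primary measures of inflammation and glutamate are *within-person differences* before and after the TSST".

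**The concern.** The share of grey matter in a spectroscopy voxel can change the glutamate reading. It is a feature of how the measurement was taken, and there is no evident reason why it should follow treatment response or 18-month course. The right question for such a covariate is whether it affects the glutamate value. Where glutamate is mediator or predictor, the stated rule asks whether it correlates with non-response or course. A covariate can explain much of the glutamate measure, fail that screen, and be left out.

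The fluid correction does not fill the gap. It divides by grey and white matter pooled, so two voxels with equal fluid but different grey/white mix get the same correction. The creatine ratio helps only so far as glutamate/creatine is the same in both tissues.

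For a change score, the quantity that matters is the difference in grey-matter fraction between the pre- and post-TSST placements. A screen on one grey-matter percentage per person does not address that difference. At stake is the precision of the estimates linking glutamate change to non-response and to course: noise in a predictor or mediator pulls its estimated effect toward zero.

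**Working it through.** **1. The plan's own sample figure.** Section 2 bases power for the logistic ridge models on N = 108, described as 90% of the sample after attrition. 108/0.9 = 120, and 120/160 = 0.75, so 108 follows from the target of 160 if attrition is 25%. That rate is inferred, since the article does not state it. The figure is not disputed and serves only as a base. With 40% non-responders (section 5), 108 splits into 43 and 65.

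**2. Size of a placement shift.** Let k be the grey:white ratio of glutamate/creatine. If grey matter is 65% of the non-fluid tissue before the stressor and 70% after, with no true change, the relative change in the measured value is (0.70k + 0.30)/(0.65k + 0.35) − 1:

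- k = 1.2: 1.14/1.13 − 1 = 0.9%
- k = 1.6: 1.42/1.39 − 1 = 2.2%
- k = 2.0: 1.70/1.65 − 1 = 3.0%

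The ratio, the 65% and the 5-point shift are all assumptions; the article gives none of them.

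**3. What the screen does when glutamate predicts non-response.** The effect detectable with 80% power at two-sided α = 0.05 (sidedness assumed) is d = (1.960 + 0.842) × √(1/43 + 1/65) = 0.551. If a share s of the variance of the glutamate measure comes from tissue, the unadjusted effect becomes 0.551 × √(1 − s).

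A simulation with 4,000 runs per setting used a linear model, with tissue unrelated to non-response and a screening cut-off of p < 0.05. The cut-off and the shares are assumptions.

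| Tissue share s | Kept by the stated rule | Kept if screened against glutamate | Power, unadjusted (closed form) | Power, stated rule | Power, always adjusted |
|---|---|---|---|---|---|
| 5% | 0.048 | 0.622 | 0.780 | 0.760 | 0.774 |
| 10% | 0.048 | 0.898 | 0.757 | 0.770 | 0.799 |
| 20% | 0.050 | 0.999 | 0.707 | 0.704 | 0.783 |
| 30% | 0.050 | 1.000 | 0.650 | 0.662 | 0.791 |

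The rule drops the covariate about 95% of the time. Power falls below that of always adjusting by 1.4 and 2.9 points at shares of 5% and 10%, and by 7.9 and 12.9 points at 20% and 30%. The simulation error of one power value is about √(0.77 × 0.23/4000) = 0.007, so the smallest gap is only roughly determined.

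**4. False positives.** With no true glutamate effect, tissue shares of 10% or 30%, and tissue differing between groups by 0, 0.2 or 0.3 SD, the rejection rate under the stated rule was 0.042 to 0.056.

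**5. Joining steps 2 and 3.** The share s is the variance due to tissue shifts divided by the variance of glutamate change. The article gives no SD for glutamate change and no placement error, so the 0.9% to 3.0% cannot be turned into a value of s. Because differencing cancels the stable part of the tissue effect, the low end of the range is the more plausible.

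**The case against.** The strongest reply is that the outcome variables in the rule may include glutamate. Section 3.6 calls the inflammation and glutamate changes the primary measures and the mood ratings tertiary outcome measures, and naming a voxel-specific covariate as the example makes most sense if glutamate is among the outcomes. On that reading grey matter is screened against the right variable. This is a fair reading, but it does not settle the matter: retention would still depend on a correlation screen, which at a 5% tissue share keeps the covariate in only 62% of simulated studies, and a person-level percentage would still not capture the pre/post difference.

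A second reply is that differencing already removes a stable additive tissue effect, and that section 3.9 uses a high-resolution anatomical image to prescribe voxels more accurately. Both points stand and limit the size of the problem.

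A third is that covariate lists by model belong in an analysis plan, which is not shown. That would answer a gap, but here the article states a rule and extends it to all analyses.

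A reader might also infer that every glutamate result in Aims 2 and 3 is affected, or that tissue mix confounds the link with non-response. The documents do not support either. In the Aim 2 group comparison, as in Aim 1, glutamate change is the dependent variable, so the rule can pick up grey matter. Placement differences unrelated to response add noise and do not bias the contrast between responders and non-responders. A systematic pre/post drift could shift the Aim 1 mean change, but that is a separate question from the screen discussed here, and the article gives no evidence of drift.

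**Conclusion.** The point holds as a minor one, confined to models in which glutamate change is mediator or predictor: the Aim 2 mediation, models predicting non-response, and Aim 3. There the rule screens a measurement covariate against the clinical outcome and will usually discard it, and nothing else in the article corrects for the grey/white mix.

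The probable consequence is some lost precision and attenuation: about 1 to 3 points of power if tissue accounts for 5% to 10% of the variance of glutamate change. Losses of 8 to 13 points need shares of 20% to 30%, which differencing makes less likely. False positives did not rise materially. These sizes rest on assumed tissue ratios, placement shifts, variance shares and screening cut-off, and on a linear model standing in for the planned ridge regression.

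**What to change.** Exempt voxel tissue fraction from the outcome-correlation screen. Pre-specify that in every model containing glutamate, the glutamate measure is adjusted for GM/(GM+WM) of its own voxel, using the pre/post difference in that fraction for change scores, whatever its correlation with non-response or course. State also whether glutamate counts among the outcome variables for the remaining covariates.

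The tissue segmentation is already needed for the fluid correction, but the change is not free:

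- **Model terms.** It takes one term per voxel and timepoint. Section 3.10 names four voxels and the mediation uses glutamate change before and after SSRI treatment, so a model with everything in it needs 4 × 2 = 8 terms. None are needed if glutamate change is first residualised on the tissue-fraction difference; in the models with a 90%/10% split, that regression should be fitted in the training part only.
- **Imaging work.** Separate pre and post fractions require each voxel placement to be registered to the anatomical image. Section 3.9 says that image is acquired at both visits, but not that one is acquired both before and after the stressor, so the imaging team should confirm that this is feasible.

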### Recruitment of target sample

3.1

Participants will be recruited through flyers posted in the community and in local clinics, UCLA data registries, and social media advertisements targeting individuals in the general Los Angeles County (including Ventura, Orange County, Riverside). The target sample for this study will be 160 treatment-seeking depressed male and female adolescents of all ethnicities ages 14–21 years old.

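### Covariates are screened on the outcome without confining the screening to the training data of the 90/10 ridge models, and the N = 108 power describes the training fit, not held-out performance

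*Protocol article*

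**What the plan says.** All the relevant text is in the statistical paragraph of the Protocol article, section Study aims & hypotheses, unless noted.

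- **Scope of the covariate rule.** It opens "For all of the statistical analyses testing these hypotheses, potential demographic (e.g., age, gender), clinical" and goes on to clinical and biological examples. Six covariates are named: age, gender, age at onset of depression, number of comorbidities, childhood trauma, and the gray-matter share of the MRS voxel. The lists are open.
- **Selection criterion.** These "covariates will be included if they are correlated with our outcome variables". The rule does not say in which participants the correlation is computed, or whether this happens before or after any split.
- **Resampling.** For the Aim 2 and 3 hypotheses that need logistic ridge regression, "we plan to sample 90% data as the training set and 10% as the testing set across 10 iterations". It is not stated whether the ten test sets are disjoint.
- **Power.** The basis is "In all simulation analyses for estimating sample size based on 1-β = 0.8". For the ridge models, "power was therefore calculated based on 90% of the sample after accounting for attrition", with N = 108. Effect sizes "were based on preliminary data or cited literature"; no values are given. Also, "Statistical significance will be set at α = 0.05".
- **Sample and event rate.** Recruitment of target sample: "The target sample for this study will be 160 treatment-seeking depressed male and female adolescents". The Discussion assumes that 40% will be treatment non-responders (TNR).

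**The concern.** A held-out set gives an honest estimate only if nothing about its outcomes entered the model. A covariate kept because it correlates with the outcome in all participants has already been chosen partly on the outcomes of those who are later used for testing. Chance correlations then reappear in the test sets and look like predictive ability. The covariate sentence covers every analysis and makes no exception for the train/test models.

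The power statement raises a second, smaller question. The split is given as the reason for calculating power at 108. Reducing N to the training fraction answers how well an association can be detected in the training data. It does not say how precisely performance in the test data will be known.

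The Discussion says the results on predictors of non-response may inform treatment guidelines. An apparent accuracy that is partly an artefact of selection, with no stated precision, would be a weak basis for that.

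**Working it through.** **1. The plan's N.** 108 / 0.9 = 120, and 120 / 160 = 0.75. So 108 is 90% of 120, and 120 is what remains of 160 after 25% attrition. The article gives no attrition rate; 25% is back-solved. With 20% attrition the training N would be 160 × 0.80 × 0.9 = 115, and with 30% it would be 160 × 0.70 × 0.9 = 101.

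**2. The plan's power.** The 80% cannot be reproduced, because no effect size is given. For scale only, at two-sided 0.05 (sidedness assumed) and 40% TNR, N = 108 splits into 43.2 and 64.8:
- standardised difference: (1.960 + 0.842) × √(1/43.2 + 1/64.8) = 0.55
- correlation: tanh(2.802 / √105) = 0.27

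Both describe an association or group difference in 108 people. Neither is a statement about held-out prediction.

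**3. Size of the optimism if screening uses everyone.** The simulation has no true signal. From the article: 40% TNR, the implied N = 120, and ten 90/10 splits. Assumed: disjoint folds, six pure-noise biomarkers always in the model, ridge penalty 5, covariates kept at about p < 0.05, AUC as the measure, 400 runs. Mean held-out AUC (Monte Carlo SE about 0.004):

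| Candidate covariates | Screened in all 120 | Screened in each training set | Difference |
|---|---|---|---|
| 6 | 0.521 | 0.499 | 0.022 |
| 10 | 0.531 | 0.493 | 0.038 (0.031 against 0.50) |
| 20 | 0.568 | 0.501 | 0.067 |

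Screening inside each training set removes the optimism. The bias grows with the number of candidates. Six is the number named as examples. The counts of 10 and 20 are assumptions, although the article mentions further covariates elsewhere: dose changes (Study design; Discussion), mood ratings (Trier Social Stress Task), and BMI, time since waking and sampling time (Inflammatory markers). Some of these are for sensitivity analyses only.

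**4. Precision of held-out performance.** If the ten test sets are disjoint, 10 × 12 = 120 out-of-fold predictions can be pooled, from 0.4 × 120 = 48 TNR and 72 responders. Hanley-McNeil variance at AUC A = 0.70:
- Q₁ = A/(2 − A) = 0.70/1.30 = 0.538
- Q₂ = 2A²/(1 + A) = 0.98/1.70 = 0.576
- variance = [A(1 − A) + 47(Q₁ − A²) + 71(Q₂ − A²)] / (48 × 72) = (0.210 + 2.278 + 6.139) / 3456 = 0.0025
- SE = 0.050

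By the same method, an AUC of about 0.65 would have 80% power against 0.50 at two-sided 0.05. These figures treat the pooled predictions as independent, which is an approximation.

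**The case against.** The strongest reply is that the leakage is inferred. The rule covers all analyses, but scope is not sequence: screening inside each training set would also satisfy the sentence, and an article may leave that order to the full plan. This stands in part. The optimism is conditional on how the rule is carried out. But the article prints an outcome-driven rule for models that are to be tested on held-out data, and the plain way to follow it is a single screen on everyone.

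The second reply is that the effect is small. With six candidates it is about 0.02 in AUC. The candidates are also not plainly noise, since the Introduction reports that earlier onset, childhood trauma and comorbidities are associated with non-response. This stands, and it favours naming those covariates in advance.

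Four stronger readings might be inferred, and the article does not support them:
- *The held-out result rests on 12 people.* One test set of 12 is very imprecise, but the plan runs ten iterations, so a single set is not the planned analysis.
- *About a third of participants are never tested.* That requires independent random draws (0.9¹⁰ = 35%). Ten test sets of 10% add up to the whole sample and fit ordinary 10-fold cross-validation. The wording is ambiguous, no more.
- *The 80% power is wrong.* The article names no held-out measure and gives no effect size, and its listed effect measures are correlations, η² and mean differences. For the model fit, 108 rather than 120 is conservative.
- *Group comparisons are restricted to 108.* The 108 is tied to the ridge analyses only.

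**Conclusion.** The point holds in a conditional form. The covariate rule selects on the outcome in all analyses and does not keep that selection inside the training data of the ridge models. If it is applied once to the full sample, null AUC is inflated by about 0.02 with six candidates and about 0.03 to 0.07 with 10 to 20. If it is repeated in each training set, there is no inflation. A reader should not conclude that leakage is certain, because the article does not state the order.

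The 80% power refers to the training-set size and does not describe held-out performance. That is a limit on what the figure means; the figure is not shown to be wrong.

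The sizes rest on these assumptions: AUC as the measure, pure-noise covariates, a p < 0.05 screen, the ridge penalty and number of biomarkers used in the simulation, disjoint folds, and the implied 120 participants. The direction of the bias does not depend on the exact settings; its size does.

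**What to change.** 1. Prespecify the covariates for the ridge models. The clinical factors that the Introduction already links to non-response are natural candidates. Otherwise, repeat the covariate screening, together with the penalty tuning, inside each training set.
2. Define the ten iterations as disjoint folds stratified by outcome, so that each participant is held out exactly once.
3. Pool the out-of-fold predictions into one named performance measure. Test it by permutation, repeating the whole pipeline (screening, tuning and fitting) in each permutation.
4. State that the N = 108 power applies to the model fit. Give separate precision for the pooled held-out measure at about 120 participants, for example an SE of about 0.05 for an AUC of 0.70 with 48 versus 72.

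This costs a little more programming and a revised power paragraph, with no change to data collection. The apparent accuracy may look less favourable than under full-sample screening.
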